### Study design

This is an open-label, individually randomised controlled trial of 200 women who have had an abnormal oral glucose tolerance test (OGTT) in their current pregnancy. Patients are randomised to the intervention (using the GDm-health management system) and half the number of clinic visits or to normal clinic care. Patient participation is from recruitment (a time point in pregnancy between 14 and 34 completed weeks of pregnancy) until delivery.

### The population studied

This trial is conducted in a large single centre tertiary referral unit in southern England. Pregnant women are screened for risk factors for GDM in their current pregnancy as per the National Institute of Care Excellence Guideline—Diabetes in Pregnancy.^5^ Women with previous GDM will be referred for a 2 h 75 g OGTT at 16 weeks and women with other risk factors for GDM are referred for an OGTT around 28 weeks of pregnancy. GDM is diagnosed by the International Association of Diabetes and Pregnancy Study Groups (IADPSG)^6^ criteria: fasting plasma BG ≥5.1 mmol/L; and/or 1 h ≥10.0 mmol/L and/or 2 h ≥8.5 mmol/L.

### Source and screening of potential participants

Pregnant women found to have GDM will be assessed by a specialist diabetes midwife. All women will be taught how to test and record their BG levels and asked to keep a food diary for 1 week. All women will be given an information leaflet about the study at their first visit. One week later, they will be assessed again in the specialist diabetes midwife clinic. At this visit, women will be given dietary advice and have baseline measurements taken (box 1). Those requiring insulin treatment for their gestational diabetes will start treatment and be referred to the consultant-led antenatal diabetes clinic. Those not requiring pharmacological treatment or only requiring oral hypoglycaemic therapy (metformin or glibenclamide) and that meet the inclusion/exclusion criteria listed in table 1 will be eligible for the trial and invited to participate. Figures 1 and 2 summarise the study selection process.
Box 1Measurements takenThe baseline measures at recruitment:
Gestational age (days)Weight (kg)AgeParityEthnicitySmoking statusHighest education levelHbA1c (%)Medication (type and dosage)Blood pressureOral glucose tolerance test resultMeasures taken at subsequent clinic visits
Glycated haemoglobinChanges to medicationWeight (kg)Maternal and fetal outcomes
Gestational age at delivery (days)Birth weight (kg)Mode of delivery (vaginal, caesarean, assisted)Severe perineal injury (binary)Shoulder dystocia/birth injury (binary)Neonatal hypoglycaemia (binary)Neonatal hyperbilirubinaemia (binary)Diagnosis of maternal pregnancy-induced hypertension or pre-eclampsia (binary)
Admission to higher level of care (maternal) (binary)Admission to higher level of care (neonate) (binary)

**Table 1 BMJOPEN2015009702TB1:** Inclusion and exclusion criteria

Inclusion criteria	Exclusion criteria
An abnormal glucose tolerance test in this pregnancy (as defined by IADPSG recommendations^6^)	Impaired cognitive function such that she is unable to operate m-health equipment
Women not requiring pharmacological treatment at recruitment	Any evidence of fetal compromise
Women started on oral hypoglycaemic therapy at recruitment	Known risk factors for obstetric complications, other than obesity and gestational diabetes
Willing and able to give informed consent for participation in the study	Gestational diabetes requiring immediate insulin treatment
Female aged between 18 and 45 years	Twins or higher order pregnancy
Singleton pregnancy	Criteria for abnormal OGTT not met in this pregnancy
Able to travel to hospital independently	OGTT result suggesting pre-existing diabetes (ie, not gestational diabetes) defined as a fasting blood glucose of ≥7.0 or 2 h≥11.1 mmol/L^10^
	Gestation greater than 34+6 at the time of potential recruitment
	Unable to speak English well enough to explain or use equipment
	Used the GDm-health system in a previous pregnancy

IADPSG, International Association of Diabetes and Pregnancy Study Groups; OGTT, oral glucose tolerance test.

**Figure 1 BMJOPEN2015009702F1:**
[figure not shown]
Flow diagram.

**Figure 2 BMJOPEN2015009702F2:**
[figure not shown]
Route of initial approach for inclusion.

### Eligibility

The inclusion and exclusion criteria are listed in table 1.

### Consent

Written informed consent will be obtained by means of a dated signature from the woman and the person who obtained the informed consent. Consent will be obtained by the chief investigator or a qualified healthcare professional with delegated authority. A copy of the signed informed consent document will be given to the woman, a further copy will be retained in the woman's medical notes and the original retained by the chief investigator.

### Randomisation

Participants will be randomly allocated to one of two groups using a partial minimisation procedure. This will adjust the randomisation probabilities between groups to balance important covariates including gestational age at recruitment (<28 or ≥28 weeks), weight at randomisation (<90 or ≥90 kg) and ethnic group (Caucasian/white or other) using Oxford University Primary Care Clinical Trials Unit randomisation system—Sortition.^21^ This is an online randomisation programme with secure access for predesignated individuals (investigators from the trial). Randomisation will be carried out at the time of recruitment by the investigators by logging onto the system to obtain the next allocation. Women will be randomised individually into the study in an equal ratio of standard care (control) to remote monitoring (intervention). Both groups will use the same glucose meter (OneTouch UltraEasy, LifeScan, Inc).

### Treatment allocation

Women will be allocated to either the standard clinic care group (control) or the remote monitoring group (intervention) (figure 3).

**Figure 3 BMJOPEN2015009702F3:**
[figure not shown]
Study overview.

BG monitoring targets, dietary advice and thresholds for starting medication will be the same for both allocation groups. All women will be asked to test their BG six times a day on at least 3 days of the week, as per the local guideline. This consists of a fasting sample, 1 h post breakfast, pre-lunch, 1 h post lunch, pre-dinner and 1 h post dinner. Optimal BG is a fasting reading ≥3.5 and ≤5.8 mmol/L and 1 h postprandial readings below 7.8 mmol/L.^11^ If there are persistently high BG readings, or medication is deemed to be required, women will be asked to increase monitoring to 7 days/week.

### Standard clinic care group

Participants in the standard clinic care group will self-record their BG values in a paper diary at home. They will be scheduled to attend the maternity diabetes clinic every 2–4 weeks where a midwife or specialist will review their readings. If, between visits, they have two or more consecutive postprandial readings ≥7.8 mmol/L or fasting readings ≥5.9 mmol/L or one reading above 9.0 mmol/L at any time of day, they will be instructed to leave a phone message for the specialist diabetes midwife. The midwife will return their call and provide further discussion and dietary advice within 72 h. If pharmacological treatment is required, the participants will be referred to the consultant-led diabetic clinic to start treatment.

### Remote glucose monitoring group

Participants in the intervention group will be given a smartphone with a preinstalled GDm-health application and Bluetooth-enabled BG meter. The research team will teach intervention participants how to use the application (figure 4). Intervention participants will be asked to attend the clinic every 4–8 weeks (ie, half as many clinic visits as the standard care group). Healthcare professionals and participants will have access to different parts of the GDm-health management system. Participants will access the front-end, an Android smartphone application and healthcare professionals will access the back-end, a server hosted within the local Trust NHS network, through a web interface. The system is described in more detail below.

**Figure 4 BMJOPEN2015009702F4:**
[figure not shown]
The GDm-health Management System.

Participants will be invited to contact the specialist diabetic midwife using a call-back request function in the smartphone application, or by phone call, if they have any concerns. A specialist diabetes midwife will review the results of the remote monitoring at least three times a week. If a participant has two or more consecutive postprandial readings ≥7.8 mmol/L or fasting readings ≥5.9 mmol/L or one reading above 9.0 mmol/L at any time of day, the specialist midwife will call the participant or send an SMS message from the web interface to the participant’'s phone inviting discussion and further dietary advice. If fewer than 12 of the minimum 18 readings a week are being done, an automatic alert will be generated on the web interface for the diabetes specialist midwife. If this alert persists for 2 weeks, the specialist diabetes midwife will contact the participant. If there is evidence that pharmacological treatment is required, the participant will be referred to the consultant-led clinic to start treatment. Further dose adjustments and messages of advice/encouragement will be communicated to the participant between clinic visits via the GDm-health management system by the specialist diabetes midwife.

Measures taken in both groups at subsequent visits and after delivery are listed in box 1.

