### Statistical analysis

#### Descriptive analyses

Baseline demographic characteristics of each group will be tabulated. The number of patients, number of missing values, the mean, range and SD of continuous variables, and the frequency of the binary variables will be reported.

The analyses will be based on the intention-to-treat (ITT) population, which will include all patients randomised. A per-protocol analysis will also be performed excluding women who did not use the GDm-health system for at least 67% of expected BG readings (at least 18 readings per week) to determine the efficacy of the system under optimal use. This level was selected as it was programmed at the beginning of the trial as the level at which the computerised system would alert healthcare professionals that a woman was non-compliant with system use.

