Gestational age at delivery (and percentage of deliveries before 37 weeks);Birth weight (and percentage of babies with birth weight above 90th centile as per the INTERGROWTH-21st Standards for gestational age and gender);Mode of delivery (vaginal, caesarean, assisted);Perineal trauma (third-degree or fourth-degree perineal tear or tear requiring suturing in the operating room);Incidence of shoulder dystocia/birth injury;Incidence of neonatal hypoglycaemia (defined as a serum BG level of <1.5 mmol/L at any time, or requiring special care baby unit (SCBU) admission for feeding);Incidence of neonatal significant hyperbilirubinaemia (defined as requiring phototherapy indicated by a serum bilirubin level of >200 μmol/L at <35 weeks, >250 μmol/L at 35–36 weeks and >300 μmol/L at ≥37 weeks);Maternal weight gain (adjusted for weeks in trial);Maternal pregnancy-induced hypertension or pre-eclampsia (defined according to the International Society for the Study of Hypertension in Pregnancy (ISSHP) criteria^23^);Admission to higher level of care for mother;Admission to higher level of care for neonate.

*Maternal and neonatal outcome analysis*: An analysis of covariance will be carried out when the outcome variable is continuous. The model will contain the term for randomisation group and baseline covariates. The results of a comparison between the two groups will be reported as a treatment effect with 95% CI. The binary variables will be analysed using logistic regression. The model will contain a term for randomisation group and baseline covariates. The results of a comparison between the two groups will be reported as an OR and a risk difference with 95% CI.

*Participants' attitudes*
Patients' attitudes will be assessed by completion of the Oxford Maternity Diabetes Satisfaction survey. This survey was developed based on several existing satisfaction surveys for diabetes management and was adapted and validated within this population.^20^ Descriptive analysis of the scores will be presented and thematic analysis of free-text comments performed.

*Compliance with the BG monitoring system*: Summary statistics will be calculated to describe the frequency of BG measurements.

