### Safety

Supervision in the form of weekly meetings with the clinicians, research team and the diabetes midwives will occur to ensure adherence to the protocol and to resolve problems and queries.

The use of self-capillary BG monitoring is well established in the pregnant and non-pregnant population. Safety concerns include adequate alerts if the remote glucose testing groups have either high or low BG readings or are not providing readings. This will be addressed by having automatic alerts activated to ensure abnormal results are not ‘missed’. The equipment to be used is a standardised, approved glucose meter with Bluetooth technology. It has been used in numerous previous studies and found to be robust. Decisions about patient care will continue to be made by trained doctors and midwives. The technology will not be relied on to automatically alert patients or provide automatic changes in management in response to the readings the system receives.

The m-health system uses a standard BG meter (OneTouch UltraEasy, LifeScan, Inc), which connects to a smartphone (HTC Desire C with Android Operating System V.4.1) via a commercially available Bluetooth adapter (Polytel Wireless Glucose Meter Accessory (GMA), Polymap Wireless LLC). The users measure their BG in the same way as usual care, but the GDm-health system allows a copy of the readings to be transmitted to the smartphone via Bluetooth. The readings are then transmitted to a secure NHS server in real time via the mobile phone data network, using checksums and encryption to ensure data integrity. The BG readings are stored in the user's meter, as well as in the smartphone memory and on the NHS server. No patient-identifiable data are transmitted between the meter and the phone or between the phone and the NHS server.

A business continuity plan has been developed to ensure women using the GDm-health system and their healthcare professionals have a contingency plan if the system fails.

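### The missing-readings alert and the per-protocol level stay tied to 18 readings a week for women moved to seven-day testing, and raw frequency does not measure compliance with the regime requested

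*Protocol article*

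**What the plan says.** Two testing schedules are set for both arms in the protocol article, under Treatment allocation (text below Figure 3). The base schedule, which follows the unit's own guidance, is (quote cut short): "All women will be asked to test their BG six times a day on at least 3 days of the week, as per the local". The intensified one is: "If there are persistently high BG readings, or medication is deemed to be required, women will be asked to increase monitoring to 7 days/week".

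Under Remote glucose monitoring group (text below Figure 4), one rule covers missing readings: "If fewer than 12 of the minimum 18 readings a week are being done, an automatic alert will be generated on the web interface". The follow-up is: "If this alert persists for 2 weeks, the specialist diabetes midwife will contact the participant". The same section provides for manual review: "A specialist diabetes midwife will review the results of the remote monitoring at least three times a week".

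Under Descriptive analyses, the per-protocol set excludes women below 67% of expected readings, with 18 a week given in brackets. The reason given is that this was programmed at the start of the trial as "the level at which the computerised system would alert healthcare professionals that a woman was non-compliant with system use".

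Under Safety: "Safety concerns include adequate alerts if the remote glucose testing groups have either high or low BG readings or are not providing readings". The next lines answer this with automatic alerts.

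Under Objectives, a secondary aim is to compare the arms on compliance with the monitoring regime assigned. Under Secondary end point analysis, the measure is: "Summary statistics will be calculated to describe the frequency of BG measurements".

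**The concern.** The number of readings requested is not constant. It rises when glucose is poorly controlled or drug treatment is needed, and women on oral therapy are eligible from the start. Yet the alert is an absolute count, the per-protocol level carries the same base of 18, and no section says that either moves with the schedule.

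Three things are at stake.

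- **The alert.** It becomes a weaker check for exactly those women who were asked to test more.
- **The per-protocol analysis.** It is meant to show efficacy when the system is used well, but it could retain women who did under a third of what was asked.
- **The compliance comparison.** A frequency has no denominator. The denominator here changes after randomisation, for reasons that may themselves depend on the arm.

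**Working it through.** **Inputs**

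- Six tests a day, on at least 3 days, or on 7 days when intensified (Treatment allocation).
- Alert below 12 of 18 (Remote glucose monitoring group).
- Per-protocol level of 67%, base 18 (Descriptive analyses).
- Assumption: six tests a day continue on the seven-day schedule. The protocol does not print a weekly total for it.

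**1. The plan's own figure.** 6 × 3 = 18 readings a week, and 12/18 = 66.7%, which rounds to the stated 67%. The alert level and the per-protocol level are therefore the same number on the base schedule.

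**2. The same count on the seven-day schedule.** 6 × 7 = 42 readings a week.

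- Alert silent at 12 readings: 12/42 = 28.6% done, 30/42 = 71.4% omitted.
- A woman who does not take up the increase and keeps to three full days: 18/42 = 42.9%, also silent.

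**3. Width of the silent range.** For comparison only, two-thirds of 42 is 28. Weekly counts from 12 to 27 are below the proportion used on the base schedule but raise no alert. If 67% is taken literally, 0.67 × 42 = 28.1 and the range extends to 28. I use two-thirds because that is what 12 of 18 is.

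**4. Sensitivity to the assumption of six a day.**

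| Tests per day on 7 days | Requested per week | 12 as a share |
|---|---|---|
| 6 | 42 | 28.6% |
| 5 | 35 | 34.3% |
| 4 | 28 | 42.9% |
| 3 | 21 | 57.1% |

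The share stays below 66.7% whenever more than 18 readings a week are requested, so the mismatch does not depend on the figure of 42. Its size does.

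**5. Per-protocol set.** If the expected number stays at 18, 12 readings meet two-thirds. Read literally, 0.67 × 18 = 12.06, so 13 would be needed, which is 13/42 = 31.0%. Either way, a woman doing under a third of 42 is retained.

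**6. Raw frequency against compliance.** 18 of 18 is 100% and 18 of 42 is 42.9%, yet both have a frequency of 18 a week. If a proportion p of an arm is on seven-day testing, the mean number requested is 18(1 − p) + 42p = 18 + 24p. If every woman did exactly what she was asked, a 10 percentage point difference between arms in p would produce a difference of 24 × 0.10 = 2.4 readings a week, with compliance identical at 100%. The 10 points are illustrative. The protocol gives no figure for p in either arm.

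**The case against.** The strongest reply is that the alert is not the only safeguard. A midwife reviews remote results at least three times a week. The web interface shows a table of all readings and a graph (Description of the GDm-health system), so sparse testing is visible. High readings prompt contact, and doses are adjusted between visits. The standard-care arm has no missing-readings alert at all. All of this stands. A reader might infer that women on medication or with poor control can under-test unnoticed between visits 4 to 8 weeks apart, and the protocol does not support that. What remains is that the high-reading rule works only on readings that were taken, and the alert is the only action stated for readings that were not.

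Second, one floor for all women can be a deliberate choice: the text speaks of a minimum, and women on seven-day testing who nearly stop are still flagged. This also stands. A reader might take the Safety section to promise an alert matched to each schedule, but it does not. It names non-provision of readings as a concern and relies on automatic alerts to meet it. The fair criticism is that this reliance is thinner on the seven-day schedule, and the text does not say whether that was intended.

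Third, a denominator for compliance is often left to the analysis plan, and Descriptive analyses already speaks of expected readings. That is partly right. But the article ties the expected number to 18, and the measure it names, frequency, differs from the objective it names. The Abstract's adjustment of the primary outcome for number of measurements does not repair a compliance comparison.

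**Conclusion.** The point holds as a mismatch between the schedules and the rules built on them. With six tests a day, 12 of 42 readings (29%) raises no missing-readings alert, and 12 to 27 a week fall below the plan's own two-thirds level unflagged. The per-protocol consequence is conditional on the expected number staying at 18, which is the natural reading of the bracket but is not stated for women on seven-day testing.

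Raw frequency does not measure the stated compliance objective. One might go on to infer that the arm with more treated women will look more compliant. That is possible but not shown: it needs a difference between arms in the share moved to seven-day testing, and the protocol gives none.

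The sample size is unaffected, and the point does not undermine the primary analysis. It concerns one automatic safeguard, a secondary outcome and the per-protocol definition, and is worth correcting on that scale.

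**What to change.** 1. Reconcile Treatment allocation, Remote glucose monitoring group, Descriptive analyses and Safety. State whether and how the missing-readings alert, and the number of expected readings, follow the seven-day schedule. If one floor for all women is intended, say so and describe the midwife review as the check above that floor. The clinical level is for the investigators to set.
2. Define compliance as readings done divided by readings requested under the schedule in force that week, and report it by arm beside raw frequency.
3. Use the same denominator in the per-protocol definition.

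The date of each schedule change has to be recorded in both arms, and if the alert is made to follow the schedule the midwife may receive some extra alerts. Items 2 and 3 need only those dates and a line each in the definitions, and can be done even if the alert software can no longer be changed.

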### Description of the GDm-health system

The development of the GDm-health system has been described previously.^8^

Each connection between the front-end (smartphone application) and the back-end (server and web interface) will be securely established on an encrypted channel and—for privacy reasons—the front-end will not contain any person-identifiable information (ie, participants will be identified by numeric ID). In order to avoid errors while reporting the BG measurement, the glucometer to be employed (LifeScan OneTouch UltraEasy) will be connected to the smartphone via a third-party Bluetooth module (Polytel Wireless GMA—Polymap). The LifeScan OneTouch UltraEasy is the glucometer of choice as it is compliant with the ISO 15197:2003 standard for blood glucose monitoring systems for self-testing in managing diabetes mellitus (this ISO standard was applicable at the time of the RCT). Readings will be transferred automatically to the Android application running on the smartphone at the time of the BG measurement, with no need of manual input.

As soon as the BG reading is stored in the smartphone's memory, the participant will be asked to ‘tag’ the reading as preprandial or postprandial through the smartphone application interface. Through the application, she will also be able to enter additional free-text comments as well as dosage and type of medication taken around the time of each reading.

All information will be transmitted to the back-end server automatically when the participant exits the application or as soon as the smartphone connects to the mobile network. The BG readings and associated information entered by the participant will be displayed together on the web interface for the benefit of the clinician reviewing the data.

Data review will be possible in two different ways: a table of all the readings taken by the patient listed in reverse chronological order and a graphical display of the readings to highlight the difference between preprandial and postprandial BG levels (values will be displayed as green, yellow or amber according to the corresponding alerting thresholds).

